#### Phase 3: Implementation and pilot of the intervention

We will pilot the theory-based knowledge translation intervention determined in Phase 2 of our work in four patient care units at the same large urban hospital used to collect our data on barriers and enablers. Routine hand hygiene audits collected by the hospital will be used to determine which units are ‘low performing.’ We will randomly select for the pilot, from all ‘low performing’ medical and surgical units, two medical and two surgical units (divided equally between campuses). We will assess effectiveness of the intervention using pre- and post-hand hygiene audits (counts of physicians/residents who washed their hands in accordance with current guidelines), which will be collected by hospital-trained auditors. We will report pre- and post-audit numbers and perform a chi-square test to examine differences between proportions of physicians/residents performing appropriate hand hygiene pre- and post- intervention if there is sufficient sample size (*i.e*., sufficient numbers of physicians/residents audited on each unit). An important element of our evaluation in Phase 3 will be a process evaluation to understand what aspects of the intervention did and did not work. The process evaluation will involve interviews with clinicians (*e.g*., physicians, residents, nurses) on the pilot units as well with hand hygiene experts across the hospital. We will conduct interviews with up to five residents and staff physicians per piloted unit. In the focus group, we will target six to eight hand hygiene experts [60]. We will follow the same process for conducting the focus groups as previously outlined. All process interviews and focus groups will be analyzed using thematic content analysis.

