## Discussion

Addressing physician behaviour is especially important given the role model and leadership roles that physicians play in healthcare settings. A better understanding of the rationale for specific physician behaviours related to hand hygiene will provide a more comprehensive framework on which to develop interventions that have a better than random chance of being successful in effecting change in this group. This can be achieved through the application of a behavioural theory approach such as that which will be applied in this study. The study presented in this protocol is based on the TDF that is derived from theories of behaviour [44]. Conducting semi-structured interviews (based on the TDF) to identify important theoretical domains to behaviour change is an approach that has rarely been used before, and to our knowledge has never been used with respect to physicians’ use of hand hygiene practice.

This study corresponds to specific aspects of the UK’s MRC framework for developing complex interventions [39,40], namely, phases 0 (problem and contextual assessment and development of the theoretical basis for an intervention), 1 (definition of components of the intervention), and 2 (exploratory studies to develop further the intervention and plan a definitive evaluative study). It is now argued that these phases should be considered as part of a larger iterative activity (as will be done in this study), rather than as sequential studies [40]. It is also believed that insights gained during these early phases of intervention development and implementation can make valuable contributions to the science of knowledge translation [40]. Upon completion of this study, we will know the barriers and enablers to physician hand hygiene compliance and have developed and piloted a theory-based knowledge translation intervention that addresses these barriers/enablers. In the future, we plan to refine the piloted intervention so it can be tested in a multi-site cluster randomized controlled trial.

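### The pilot's only named inferential analysis is a chi-square test run if numbers are sufficient, with no threshold given; the pre-post difference should always be estimated with an interval

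*Protocol article*

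**What the plan says.** The section *Phase 3: Implementation and pilot of the intervention* gives the purpose of the audits: "We will assess effectiveness of the intervention using pre- and post-hand hygiene audits". The outcome data are "counts of physicians/residents who washed their hands in accordance with current guidelines", collected on two medical and two surgical units.

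The analysis is given in one sentence. It opens "We will report pre- and post-audit numbers and perform a chi-square test", and the test, which compares the pre and post proportions, is made conditional: "if there is sufficient sample size". The explanation of that condition is "sufficient numbers of physicians/residents audited on each unit". No number follows.

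The section then adds a qualitative strand that does not depend on audit numbers: "An important element of our evaluation in Phase 3 will be a process evaluation".

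The *Discussion* states the next step: "we plan to refine the piloted intervention so it can be tested in a multi-site cluster randomized controlled trial". It also places the study in the exploratory phase of the MRC framework, which covers both developing the intervention and planning a definitive study.

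**The concern.** There are two linked weaknesses, and both lie in what the text fixes.

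- **The condition has no content.** The authors chose to make the test conditional and to explain the condition, but the explanation only repeats the word *sufficient*. It does not say whether the standard is validity of the chi-square approximation, adequate power or something else. It is also unclear whether each unit must meet the standard alone or only contribute to a pooled total.
- **The named method answers the less useful question.** A chi-square test indicates whether the pre and post proportions differ by more than chance. It does not say by how much, or how precisely this is known. With four units and a cluster randomized trial to follow, the useful quantities are the size of the change, its uncertainty and how far the units differ from one another.

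At stake is a pilot whose quantitative result could take quite different forms depending on a decision that the plan does not pin down.

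**Working it through.** **No figure to reproduce.** The article states no sample size, significance level, power or target effect for Phase 3. The calculation below only shows how much room the word *sufficient* leaves.

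**Inputs from the document**
- Hospital-wide physician compliance of 65–69% in March 2011, and a corporate goal of 80% (*Background*).
- Four pilot units chosen from those classed as low performing (*Phase 3*).

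**Assumptions not in the document**
- Two-sided 5% level and 80% power.
- Equal numbers before and after.
- Independent observations, with no clustering by unit and no repeat audits of the same physician.
- Main illustration: p₁ = 0.65 before and p₂ = 0.80 after, so the mean proportion is p̄ = 0.725.

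**Reading 1: *sufficient* means that the chi-square approximation is valid.** The smallest expected cell is n(1 − p̄). With n = 20 per period it is 20 × 0.275 = 5.5, which passes the usual rule of at least 5.

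**Reading 2: *sufficient* means 80% power.**

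n = [1.96√(2p̄(1 − p̄)) + 0.842√(p₁(1 − p₁) + p₂(1 − p₂))]² / (p₂ − p₁)²

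= [1.96 × 0.6315 + 0.842 × 0.6225]² / 0.15² ≈ 138 per period (151 with continuity correction).

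The two readings differ by a factor of 138/20 = 6.9.

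**Range over the starting rate**, for a rise to 80% (continuity-corrected figure in brackets):

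| Starting rate | Audits per period |
|---|---|
| 50% | 39 (45) |
| 60% | 82 (91) |
| 65% | 138 (151) |
| 67% | 180 (195) |
| 69% | 246 (264) |

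The two lowest rows allow for low-performing units starting below the hospital average.

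**What a p-value would hide.** The 95% half-width for the difference is 1.96√[(0.65 × 0.35 + 0.80 × 0.20)/n] = 1.96√(0.3875/n):

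| n per period | Power | Half-width (points) |
|---|---|---|
| 20 | 18% | ±27 |
| 50 | 39% | ±17 |
| 100 | 66% | ±12 |
| 138 | 80% | ±10 |
| 200 | 92% | ±9 |

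An assumed change of 15 points would carry an uncertainty of 27 points either way at the smallest of these sizes and 9 at the largest.

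**Per unit or pooled.** If 138 were a pooled requirement, it would mean 138/4 ≈ 35 audits per unit per period. If each unit had to meet it, the total would be 4 × 138 = 552 per period. The explanation refers to each unit, but the test is described in the singular, so the text does not settle which is meant.

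Clustering within units and repeat audits would change all these figures. The document gives no intracluster correlation, so no adjustment is attempted.

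**The case against.** The strongest reply is that this is a small exploratory pilot described in a journal article, and that declining a chi-square test on small counts is ordinary good practice. That is fair, and it limits the point in several ways.

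- **A reader might infer that the pilot could end with only a p-value, or with no quantitative result.** The text does not support this. On its natural reading the condition governs only the test, and the audit numbers are reported regardless. If numerators and denominators are given, a crude difference can be derived. The process evaluation also goes ahead whatever the numbers.
- **A reader might infer that no interval will be calculated.** The article is silent on this. It condenses a fuller document, and interval reporting may stand in an analysis plan that is not shown. What can be said is that the article names none.
- **A reader might infer that sufficiency will be judged after the results are seen.** The text does not say when it is judged, and its explanation refers to numbers audited, not to compliance. A condition on denominators does not by itself select on outcome. But without a threshold, nothing in the text rules out deciding with the results in view.
- **A reader might infer four separate unit tests and a multiplicity problem.** The text speaks of a single test, and mentions each unit only in describing where numbers must suffice.
- **The *Discussion* does not say that the pilot will supply an effect size or variance for the later trial.** An uncontrolled change in units chosen for low performance would be a weak basis for a target effect in any case. The article does place the study in a phase meant for planning a definitive evaluation, so precision and between-unit spread remain relevant.

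One thing stands after all this: a stated decision rule without a criterion, attached to a method that does not estimate the change.

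**Conclusion.** The point holds as a minor improvement. The article sets out to assess effectiveness, names one inferential analysis, and makes it depend on a condition that it does not define. Beyond that it promises only the pre and post numbers, and it does not say that these will be given by unit.

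Under the illustrative 65% to 80% change with independent observations, two ordinary meanings of *sufficient* lie about sevenfold apart (20 against 138 audits per period), with power of 18% against 80%. These figures show how loose the criterion is. They do not show an error in any number that the plan states, and they rest on an assumed level, power and starting rate.

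**What to change.** Remove the condition and make estimation the planned quantitative result:

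1. For each of the four units, report the pre and post counts, the proportions and the pre-post difference with a 95% confidence interval, using an exact or score-based method where counts are small.
2. Show the spread of the four unit differences.
3. Give an overall difference with an interval that allows for clustering by unit. One simple choice is the mean of the four unit differences with a t interval on 4 − 1 = 3 degrees of freedom: mean ± 3.18 × s/√4, or mean ± 1.59s, where s is the standard deviation of the four differences. An overall exact or score interval on pooled counts would ignore clustering and could be too narrow.
4. Treat any p-value as descriptive.

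**Cost:** a few lines of analysis wording, with no new data collection provided that the audit counts can be tabulated by unit. The overall interval will be wide, because the multiplier on 3 degrees of freedom is 3.18 instead of 1.96, and the result may look less favourable than a pooled test would.

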#### Ethics

Ethical approval for this study was obtained from the Ottawa Hospital Research Ethics Board (protocol # 2012040801H). Operational approval was obtained from The Ottawa Hospital.

## Discussion

Addressing physician behaviour is especially important given the role model and leadership roles that physicians play in healthcare settings. A better understanding of the rationale for specific physician behaviours related to hand hygiene will provide a more comprehensive framework on which to develop interventions that have a better than random chance of being successful in effecting change in this group. This can be achieved through the application of a behavioural theory approach such as that which will be applied in this study. The study presented in this protocol is based on the TDF that is derived from theories of behaviour [44]. Conducting semi-structured interviews (based on the TDF) to identify important theoretical domains to behaviour change is an approach that has rarely been used before, and to our knowledge has never been used with respect to physicians’ use of hand hygiene practice.

This study corresponds to specific aspects of the UK’s MRC framework for developing complex interventions [39,40], namely, phases 0 (problem and contextual assessment and development of the theoretical basis for an intervention), 1 (definition of components of the intervention), and 2 (exploratory studies to develop further the intervention and plan a definitive evaluative study). It is now argued that these phases should be considered as part of a larger iterative activity (as will be done in this study), rather than as sequential studies [40]. It is also believed that insights gained during these early phases of intervention development and implementation can make valuable contributions to the science of knowledge translation [40]. Upon completion of this study, we will know the barriers and enablers to physician hand hygiene compliance and have developed and piloted a theory-based knowledge translation intervention that addresses these barriers/enablers. In the future, we plan to refine the piloted intervention so it can be tested in a multi-site cluster randomized controlled trial.

A limitation to this study will be measurement of the target behaviour (*i.e*., measurement of hand hygiene compliance). There are three main methods for measuring hand hygiene performance, each of which has advantages and disadvantages: directly observing, measuring product use, and self-report. Direct observation of hand hygiene behavior of HCWs chosen for this study is considered the ‘gold standard’ of measurement methods. It allows you to see which hand hygiene products are used, the thoroughness of cleansing, and importantly, whether the staff is performing hand hygiene whenever there is an opportunity to do so. This method also allows observers to give prompt feedback about whether improvement is needed. On the other hand, direct observation is also labor intensive and expensive, requiring the careful selection and training of those who will observe and record data. It can also influence the behavior of those who know they are being observed, which is a potential bias in our study. The success of this method depends on the accurate calculation of adherence rates, the careful training of data collectors, and the data collectors’ uses of clear, easy-to-understand forms. Therefore, in an attempt to limit bias, we will use hospital-trained auditors.
